**Trial registration:**

NCT04911179 02/06/2021.

**Supplementary Information:**

The online version contains supplementary material available at 10.1186/s12877-022-03214-0.

## Introduction

### Background

Approximately, 1 out of 3 adults aged 65 or over experience at least one fall per year and among them, 10% suffer a significant injury such as a fracture or traumatic brain injury [1]. These figures rocket in those aged 80 years or more, with half of them falling over the course of a year [2]. Around 10% of falls result in a fracture [3, 4]. In the European Union, it has been estimated that 36,000 older adults die because of a fall yearly, whereas the figures of hospital admission and emergency department visits approximate to 1.5 million and 2.3 million, respectively [5].

Although most fall-related injuries (bruising, lacerations, sprains…) are not severe, they represent important drivers of decline of the intrinsic capacity (physical and cognitive capacities of the individual) [6], functional limitations development, reduced quality of life and the development of psychosocial issues (anxiety, fear of falling and depression) [7, 8]. Therefore, falls constitute a significant sentinel event for older adults by threatening their health and well-being. With the population of older adults increasing worldwide [9], falls will continue to represent an increasing health and economic burden on the public health system. Consequently, prevention of falls has become an international public health priority [10, 11].

Most of the clinical practice guidelines recommend managing older frail adults with repeated falls in specialized Falls and Fracture Units [12]. Ideally management of falls should consist of a multidimensional comprehensive assessment [13] followed by tailored multidomain interventions lead by an interdisciplinary team (physician, nurse, physiotherapist and occupational therapist) and focused to identify and tackle risk factors [12, 14].

Among them, progressive cognitive and physical function decline stand out, both as targets of falls preventive and mitigating interventions, given their tight relation with their occurrence [15–17]. Impairments in the physical domain, such as muscle strength [18], gait performance [19] and balance [20], are strong risk factors for falls, whereas decreases in the cognitive abilities, especially in the executive function domain [21], have been associated with the odds of falling [22] and suffering fall-related injuries [23]. Executive function is a cognitive domain composed of a broad set of cognitive processes integrating information from multitude cortical systems to generate goal-directed behavior [24]. It constitutes an integral function and one of the most important components of daily-living navigating [25]. In addition, robust evidence supports the relationship between cognition and motor function, with common anatomical substrates and neural pathways. Allocated in the prefrontal cortex, executive functions play a key role in neural control of gait [26, 27], especially under challenging circumstances. For instance, when an attention-demanding cognitive task is performed during a walking task, known as dual-task, the performance of either one or both tasks may decrease compared to each individual task as a result of competence for common neural pathways [28]. This motor-cognitive crosstalk also explains the higher risk of falls among persons with cognitive and physical impairment, therefore interventions targeting both might be key to reduce falls risk [29].

Loss of capacities constitute manifestations of the progressive loss of reserve at multi-systemic physiological levels, leading to increased vulnerability when facing stressors, a state that was decades ago termed frailty [30–32]. Frail individuals present with the highest risk of suffering falls and related outcomes [33, 34]. Consequently, frail individuals might benefit the most from interventions oriented to falls prevention trough combined interventions, but the number of studies in this population is limited [35].

In this sense, physical exercise stands out as an effective cornerstone in falls prevention among geriatric patients [13, 36]. Exercise has been shown to concurrently positively impact both physical and cognitive function of older adults [37–40], which might result in the observed reductions in the risk and rate of falls both in community-dwelling [41, 42] and residential populations [43]. In addition, exercise has shown to beneficially impact fall-related issues such as fear of falling [44]. Previous evidence has shown that multicomponent physical exercise programs combining strength and balance exercises might confer the greatest benefits in older adults with high risk of falling [36, 42]. Nevertheless, so far, the features of an exercise program as a single intervention that might maximize effectiveness remain to be elucidated [36].

Given that cognitive impairments are associated with falls occurrence [45], cognitive training, usually involves a guided practice on a set of specific tasks designed to engage targeted cognitive functions [46], might be beneficial in falls prevention [47]. Cognitive training interventions like dual task training, improve attention, executive function and memory in older persons with cognitive decline but also in healthy older adults [48]. A reduced number of emerging studies have shown cumulative effects in fall risk parameters of combined exercise and cognitive training interventions compared to interventions focused exclusively in motor function [49]. Both animal- and human-based studies have shown greater neurophysiological (neurogenesis, neuroplasticity and increased brain blood flow) and functional (physical and cognitive performance) [50, 51] after the combined intervention, compared to single intervention-based approaches [52, 53]. Putatively, programs combining physical exercise and cognitive training focused in executive function tasks might constitute the optimal approach to maximize reductions in fall risk and associated complications [12, 54], but whether available evidence translate to reductions in falls incidence remains to be elucidated [55, 56].

The OTAGO exercise program (OEP), that was developed in the 1960s in New Zealand [57], is considered the gold-standard exercise-based intervention in falls prevention. It consists of several strength, endurance, flexibility and balance exercises supervised by a physical therapist. It has shown to be effective in improving fall-related risk factors [58–60] and preventing falls [61, 62] and related consequences [63, 64]. Notably, several adaptations have been performed since it was firstly designed, leading to a high degree of heterogeneity, with mixed results obtained from different delivery fashions [65–67]. In addition, falls and fall-related outcomes have been poorly registered in available studies, and how exercise programs impact fall-related fractures, healthcare utilization, psychological and social issues remains scarcely investigated [68]. Consequently, well-powered studies with long follow-up periods and comprehensive evaluation of falls consequences are needed in order to capture the real potential of exercise programs in different populations of older adults [42].

Recently, the VIVIFRAIL Project (www.vivifrail.com) was developed by world experts in the field of physical exercise and frailty aiming to provide necessary knowledge to prescribe individualized physical exercise in the prevention of frailty and falls in older persons. Within the VIVIFRAIL philosophy, exercise prescription is based on the functional status and fall risk of the individual, evaluated through performance-based measures [69]. This approach aligns with the recently proposed function-based healthy ageing paradigm [70]. So far, this exercise program has been proven safe and effective to reverse the hospitalization-associated functional decline in very old patients [71] and to promote functional gains in cognitively impaired frail community-dwellers [72], but its effectiveness to reduce falls and health related-consequences, and whether its combination with cognitive training have added effects remain uncertain.

In this context, the main objective of this study is to evaluate the effectiveness of a combined individualized multicomponent exercise and cognitive training (VIVIFRAIL-COGN) program on the reduction in fall-incidence in a sample of community-dwelling frail older adults with high fall risk, compared to usual care (including the OEP). Secondarily, we will investigate the impact on fall-related consequences, such as need for medical assistance, psychological issues (fear of falling and depression), physical and cognitive capacities and quality of life.

## Methods

### Study design and setting

The present study is a multicenter randomized clinical trial to be conducted in the Falls Unit of the geriatrics department of four tertiary hospitals in Spain. Its main aim will be to explore the effectiveness of a multicomponent exercise program combined with a cognitive stimulation program in the reduction of falls and related outcomes among frail older adults. Falls units are specialized clinical environments, to which older adults with recurrent falls are referred from Primary Care or other medical specialties. In these Units, falls etiology and potential management are studied by a multi-disciplinary team. Interventions include physical exercise programs, polypharmacy reduction, environmental adequation in accordance with published international and national guidelines [73].

Patients who meet the inclusion criteria for this study will be randomly assigned to usual care or an intervention consisting in the combination of individualized exercise and cognitive stimulation program. Prior to randomization, the attending geriatrician will review the absolute and relative contraindications to participate in exercise programs and will provide general information about the study. Patient recruitment will begin with the normal visit of the patient to the clinic, in which inclusion criteria will be ascertained and informed consent obtained. Later, subjects will be randomly assigned (as explained later) to either the intervention or the usual care (control group).

### Study participants and eligibility criteria

The study will include outpatients of the Falls Units of the University Hospital of Navarra in Pamplone, the Hospital of Guadalajara, the Hospital Perpetuo Socorro in Albacete and the Parc Sanitari Pere Virgili in Barcelone (all in Spain) recruited between June 2021 and August 2023. Inclusion criteria include:

Age ≥ 75 years or olderReferral to the Falls UnitAbility to ambulate independently with or without technical aidsBarthel Index ≥ 60Pre-frailty (1–2 criteria) or Frailty according to the Frailty Phenotype by Fried et al. [30]High risk of falling defined by one or more of the following criteria

Gait disorders captured through physical performance measures (Time Up and Go Test ≥ 20 s and/or Usual Gait Speed (GS) < 0,8 m/s [74] ≥ 2 self-reported falls in the previous year≥ 1 self-reported falls requiring medical assistance in the previous year

Relative/caregiver willingness to supervise the exercise/cognitive stimulation sessionsCapability and willingness to provide informed consent

### Subjects will be excluded from participation based on the following exclusion criteria

Unwillingness to either complete the study requirements or to be randomized into the control or the intervention groupLife expectancy ≤ 3 monthsTerminal illnessNo possibility of follow-upInstitutionalization or awaiting institutionalizationMajor cognitive disorder according to GDS Reisberg (GDS) classification: 5 or higherSevere visual o hearing deprivationAny contraindications for physical exercise or testing procedures, including but not limited to:
myocardial infarction in the past 3 monthsunstable angina pectorisuncontrolled arrhythmiaunstable cardiovascular disease or other unstable medical conditionuncontrolled arterial hypertensionrecent pulmonary thromboembolismupper or lower extremity fracture in the past 3 months

### Randomization and blinding

Included subjects will be randomized by using a randomization list generated electronically (www.randomizer.org) into the combined intervention group and the usual care group (control group) following a simple randomization procedure, in a 1:1 ratio without restriction. Participants will be explicitly informed and reminded not to disclose their randomization assignment to the assessment team, which will be blinded to the participants’ group membership. It will not be possible to conceal the group assignment from the staff involved in the training of the intervention group. Patients (or their families) will be informed of their random inclusion in one group but will not be informed regarding to which group they belong.

### Data collection

Data from both the combined intervention and the usual care group will be obtained by the research team (physiotherapist, sport sciences specialist and geriatrician) at three different times: at baseline (T0) and at the 6-week (T1) and 12-week (T2) follow-up visits (Fig. 1). A telephone-based follow-up visit, and a review of the electronic clinical chart will be conducted at 6, 9 and 12 months after the start of the participation for gathering data on falls incidence, functional status and exercise continuation (Table 1). All adverse events, including those related to exercise such as muscle pain, fatigue and general aches and pain, will be recorded in an “adverse events diary” during follow-up visits and telephone calls by the training and testing staff, and by self-report during the study period.

**Fig. 1 Fig1:**
[figure not shown]
Flow diagram of the study protocol

**Table 1 Tab1:** Study timeline

	**Screening**	**T0** **Basal**	**T1** **6 W**	**T2** **12-W**	**T3** **6 M**	**T4** **9 M**	**T5** **12 M**
***Primary outcome***							
Number of self-reported falls		X	X	X	X	X	X
**Secondary outcomes**							
Risk of falls Usual Gait Speed (UGS) Time up and Go (TUG)	X			X			
Short Physical Performance Battery (SPPB)		X	X	X			
Barthel index (BI)	X		X	X	X	X	X
Frailty Linda Fried criteria	X			X			
Montreal Cognitive Assessment (MoCA)		X	X	X			
Garvan fracture risk calculator		X		X	X	X	X
Yesavage GDS Scale		X		X	X	X	X
UGS with dual tasking		X	X	X			
Clinical criteria of sarcopenia		X		X			
Maximal isometric force of handgrip, knee extension and hip flexion		X	X	X			
Fear of falling (STAC)		X		X	X	X	X
Quality of life (EQ-5D)		X		X	X	X	X
Previous lifestyle		X					
Trail Making Test (TMT – Part A)		X	X	X			
1RM (Leg press)		X	X	X			
Muscular power at 50% 1RM in leg press		X	X	X			
Polypharmacy		X		X	X	X	X
Cumulative Illness Rating Scale for Geriatrics (CIRS-G)		X					
Mini Nutritional Assessment Test (MNA)		X					
Acceleration data: gait kinematic parameters (regularity, variability, cadence), Five Times Sit to Stand Test (peak power, impulse) and balance parameters (power spectrum, area)		X	X	X			
Muscular Echo intensity and thickness (ultrasound)		X		X			
Mortality		X	X	X	X	X	X
Admissions to emergency room and hospitalizations		X	X	X	X	X	X
Institutionalization		X	X	X	X	X	X

The multidisciplinary research team have well-known previous experience in functional geriatric assessment and in the prescription of exercise in frail aged participants in different clinical settings [71, 75, 76].

### Sample size and statistics

Study main outcome is the falls rate/year. For its estimation we will use a negative binomial distribution (over-dispersed Poisson distribution). Assuming an alpha error of α = 5%, an average fall rate of 1,8 falls/year in the usual care group and a mean follow-up of 0.9 years, the sample size required for each group will be 129 to have an 80% power to detect a 30% reduction in the one-year fall rate in the combined intervention group. Considering a withdrawal of 20% during the follow-up, the final simple size per group will be 155. Assumptions are based on results from the Actions Seniors Secondary Falls Prevention in Community Senior Fallers Study [77].

All the participant centers have a remarkable clinical activity attending around 1000 patients every year. It is expected than 15% of these patients in every center can be potentially eligible participants. If not reaching the defined sample size, the inclusion period will be extended for a further 3 months.

Baseline characteristics of the sample will be described by using the central tendency (mean and median) and dispersion (standard deviation, standard error, interquartile ranges and confidence intervals) for continuous variables and absolute (counts) and relative (percentages) frequencies for categorical variables. For comparisons between groups at baseline, t tests or Mann–Whitney U tests will be used for continuous variables, upon normality, which will be checked for each using the Kolmogorov–Smirnov test and normal probability plots, and the chi-square test or Fisher’s test will be used for categorical variables.

Main analyses will focus on the detection of differences in the rate of falling between groups. Study main outcome is the fall rate/year. For its estimation we will use a negative binomial regression (Poisson model extension that allows for the presence of overdispersion). Randomization group will be included as the exposure and factors potentially distorting the estimations as covariates. Robust standard errors consistent with heteroskedasticity will be employed by using the “sandwich” package in R (R 3.4.1 (R Core Team, Vienna, Austria). Falls incident rate ratios and their 95% confidence intervals will be estimated by model coefficients and absolute in the rates will be estimated from the results.

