**Methods:**

This study is designed as a four-center randomized clinical trial with a 12-week intervention period and an additional 1-year follow-up. Three hundred twenty frail or pre-frail (≥ 1 criteria of the Frailty Phenotype) older adults (≥ 75 years) with high risk of falling (defined by fall history and gait performance) will be recruited in the Falls Units of the participating centers. They will be randomized in a 1:1 ratio to the intervention group (IG) or the control group (CG). The IG will participate in a home-based intervention combining the individualized Vivifrail multicomponent (aerobic, resistance, gait and balance and flexibility) exercise program and a personalized executive function-based cognitive training (VIVIFRAIL-COGN). The CG group will receive usual care delivered in the Falls Units, including the Otago Exercise Program. Primary outcome will be the incidence of falls (event rate/year) and will be ascertained by self-report during three visits (at baseline, and 6 and 12 weeks) and telephone-based contacts at 6, 9 and 12 months after randomization. Secondarily, effects on measures of physical and cognitive function, quality of life, nutritional, muscle quality and psychological status will be evaluated.

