### Trial status

The trial began recruitment in July 2021 and is currently open for recruitment. Recruitment will cease when 310 participants have been randomized. It is anticipated that this target will be reached by September 2023.

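### The 20% withdrawal allowance multiplies 129 by 1.2 instead of dividing by 0.8, so 155 per group retains 124 rather than 129; the abstract's total of 320 also conflicts with 310 elsewhere (minor)

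*Protocol article*

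**What the plan says.** The section on sample size and statistics fixes the size in two steps. First comes the number needed for power: "the sample size required for each group will be 129 to have an 80% power". Its inputs are "an average fall rate of 1,8 falls/year in the usual care group", "a mean follow-up of 0.9 years", a 30% reduction in the rate and a 5% alpha, under a negative binomial model. No dispersion value is printed, and the test is not said to be one- or two-sided. The second step allows for losses: "Considering a withdrawal of 20% during the follow-up, the final simple size per group will be 155".

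Two other places give a total. The abstract, under Methods, opens its description of the sample with "Three hundred twenty frail or pre-frail" older adults. The Trial status section says "Recruitment will cease when 310 participants have been randomized". Allocation is 1:1, so 155 per group also means 310.

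**The concern.** An allowance for withdrawal should ensure that the required number remains once the stated proportion has left. Multiplying by 1 plus the withdrawal proportion does not do that; dividing by 1 minus the proportion does. The protocol's figure matches the first operation, so the number it prints does not retain the number it says it needs.

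The total matters in practice. It ends recruitment, and the sample size section also provides for a three-month extension if the planned size is not reached. At 310 randomized, recruitment is complete according to Trial status and ten short according to the abstract.

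**Working it through.** **Inputs, all from the sample size section unless noted.** Required number per group 129; withdrawal 20%; final number per group 155; control rate 1.8 falls per year; rate ratio 1 − 0.30 = 0.70; mean follow-up 0.9 years; alpha 5%; power 80%. Totals: 320 (abstract) and 310 (Trial status).

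**Step 1: reproduce 155.** 129 × 1.20 = 154.8, rounded up to 155. This matches the protocol exactly.

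**Step 2: the allowance that retains 129.** n / (1 − d) = 129 / 0.80 = 161.25, rounded up to 162 per group, or 324 in total. Check: 162 × 0.80 = 129.6, which meets 129.

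**Step 3: what the printed figures retain.**

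| Per group | Total | Left after 20% loss | Against 129 | Withdrawal covered |
|---|---|---|---|---|
| 155 | 310 | 124 | 5 short | 1 − 129/155 = 16.8% |
| 160 | 320 | 128 | 1 short | 1 − 129/160 = 19.4% |
| 162 | 324 | 129.6 | met | 1 − 129/162 = 20.4% |

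Steps 1 to 3 need no assumption about dispersion or about the test.

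**Step 4: what this could mean for power (illustration only).** The protocol gives no dispersion k, so 129 cannot be confirmed independently. I assume a two-sided 5% test and the Wald formula for a log rate ratio:

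n = (1.960 + 0.8416)² × [(1/t)(1/1.8 + 1/1.26) + 2k] / (ln 0.7)²

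Here 1.26 = 1.8 × 0.7, (1.960 + 0.8416)² = 7.849 and (ln 0.7)² = 0.1272.

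- At t = 0.9 the first term in the bracket is 1.349 / 0.9 = 1.499. Setting n = 129 requires a bracket of 129 × 0.1272 / 7.849 = 2.091, so k = (2.091 − 1.499) / 2 = 0.296.
- Other choices for the variance under the null move the back-solved k up to 0.39.

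Power = Φ(√n × 0.3567 / √bracket − 1.960), with k = 0.296:

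| Analysed per group | Follow-up | Bracket | Power |
|---|---|---|---|
| 129 | 0.9 years | 2.091 | 80.0% |
| 124 | 0.9 years | 2.091 | 78.4% |
| 124 | 1.0 year | 1.349 + 0.592 = 1.941 | 81.3% |
| 155 | 0.9 years (mean) | 2.091 | 86.7% |

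Across the variance choices, each with its own back-solved k, power is 78.4% to 78.5% for 124 at 0.9 years and 86.4% to 86.7% for 155 at 0.9 years.

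**The case against.** The best defence is that the planned analysis models a fall rate. Such a model can use the follow-up that withdrawn participants contribute before leaving, and falls are collected at several contacts over the year. If all 155 are analysed at a mean of 0.9 years, the illustrative power is well above 80%. This stands as a reason to call the consequence small. It does not rescue the printed step, because the protocol presents the 20% as a separate loss on top of 129 and does not justify 155 by retained person-time.

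Three stronger readings are tempting.

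- **Withdrawal has been counted twice.** A reader might note that 20% leaving at uniform times over a year gives a mean of 0.8 × 1 + 0.2 × 0.5 = 0.9 years, exactly the follow-up assumed. The protocol does not say where 0.9 comes from; it attributes its assumptions to an earlier falls trial, and other explanations are possible. A matching sum is not evidence, so this is a question for the sponsor.
- **The trial is underpowered at 78%.** That figure combines an outright 20% loss with 0.9 years among those who remain. If 0.9 already reflects withdrawal, the completers have a full year and 124 of them give about 81%. The 78% figure and the double-counting argument therefore cannot both hold. Every one of these percentages also depends on a dispersion solved backwards from 129.
- **The trial has two competing targets.** The only explicit stopping number is 310, and it agrees with 155 per group. The abstract alone differs, which makes this a consistency slip.

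**Conclusion.** Wrong as written, and minor. The protocol's 155 per group does not retain its own 129 after its own 20% withdrawal: it retains 124, and 162 would be needed. The abstract's 320 contradicts the 310 given by the other two places and also falls short, by one per group. These conclusions rest only on printed figures.

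The size is five retained participants per group, or seven randomized per group (14 in total against 310). In power, the loss is about 1.6 points on the least favourable reading, and there may be no loss at all if withdrawn participants contribute person-time or if 0.9 years already includes withdrawal. That part assumes a two-sided test and k of about 0.30. The estimand, the analysis model and the treatment are unaffected.

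**What to change.** Use one total throughout. The cheapest course keeps 310:

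1. Change the abstract from 320 to 310.
2. In the sample size section, either state that 155 per group covers about 17% withdrawal while retaining 129, or restate the power for 155 from the sponsor's actual dispersion value. In the second case, print that value, say whether withdrawn participants contribute person-time, and say whether the 0.9-year mean follow-up already includes withdrawal. The percentages above are illustrative and should not be copied into the protocol.

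This costs a few words and no participants. If the intention is to retain 129 per group after an outright 20% loss, print 162 per group and 324 in total in the abstract, the sample size section and Trial status. That costs 14 more participants than 310.
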